#### Mediator and Moderator Analyses

Potential mediators and moderators of the efficacy of the intervention will also be explored. For example, level of program engagement, defined by number of sessions completed and number of days logged on to the program, will be evaluated for mediation of outcomes.

Additionally, given that randomization was stratified between clinical and subthreshold populations, whether symptom severity influences the efficacy of the intervention to reduce GAD symptoms can be explored. Additional predictors of outcome that will be explored include medication use, motivation to work on anxiety, belief in efficacy of online programs, perceived social support, and grade point average. Medication use will be controlled for in the analyses if the sample is large enough; otherwise, the results will be provided qualitatively.

## Results

The study commenced in February 2015. The sample was recruited over a 3-week period at each college. The trial is expected to end in December 2015.

## Discussion

### Potential Impact

This trial represents an opportunity to explore whether technology can be leveraged to reduce the significant mental health treatment gap in India, particularly for students in Indian universities. This will be the first trial to examine the feasibility, acceptability, and efficacy of Internet-based, unguided and guided self-help interventions to reduce GAD symptoms in Indian university students. It will also be the first trial evaluating the acceptability and feasibility of online, guided self-help interventions supported by trained mental health workers in India.

Intervening to reduce GAD symptoms in students is important because increasing GAD symptomatology is associated with greater functional impairment [11], reduced quality of life [12], greater disability and help seeking [13,14], and greater costs of health care [15]. Furthermore, without treatment, GAD symptoms have a chronic course and persistent symptoms [9]. Given the increasing prevalence of Internet connectivity and mobile phone penetration [69] and in the face of limited mental health care professional availability, delivering evidence-based mental health care via the Internet may be particularly attractive to individuals in developing countries, particularly students in Indian universities, who have limited access to mental health care services. Furthermore, both programs that will be employed, GAD Online and Lantern, are scalable platforms, thus making the use of Internet-based, unguided and guided self-help interventions a practical approach. If the interventions are found to be effective, these programs can be more specifically adapted for this population and then be promoted and disseminated seamlessly to the larger student population, universities, and younger individuals.

### Limitations

Relying entirely on self-report data to assess individuals is a limitation of this study and implies that the allocation of interventions may not be as reliable as if diagnostic interviews and other objective measures were used. This method was selected for two reasons. First, one of the primary barriers to help seeking is stigma, particularly in this population. In stakeholder discussions, both administrators and students highlighted that concerns around confidentiality and disclosure to others – peers, professors, parents – prevent many students from visiting the existing on-campus counselor. Thus, a private, entirely online approach is likely to achieve greater participation and more accurate responses. Second, one of the main goals of this model of intervention is to develop a cost-effective and sustainable way to disseminate and evaluate these programs at scale, and requiring an in-person assessment would dramatically increase costs and reduce sustainability. Moreover, these assessments are meant to inform recommendations about program "matches" that meet participants' self-reported needs, and participants are empowered to choose the avenue of support they perceive to be the best fit (ie, on-campus counselor or online program). Following initial trials establishing feasibility, clinical interviews can be conducted along with self-report assessments to evaluate the validity and reliability of the self-report screening measures for this population. Additionally, in future trials, the real and important limitation of response burden could be addressed and fewer, more targeted measures could be administered.

Another limitation is that the primary outcome measurement tool, the GAD-Q-IV, and the associated diagnostic thresholds have been normed in US university student populations but not in an Indian university student population. One implication is that the prevalence of the disorder could be mischaracterized due to diagnostic criteria being interpreted differently cross-culturally. For example, the DSM-IV GAD criterion that anxiety be “excessive” might lead to underdiagnosis of GAD in developing countries in which worry is less likely to be reported excessive in the presence of comparatively more severe life concerns [70]. Using dimensional versus categorical scoring of the GAD-Q-IV to both determine eligibility and monitor for change in symptomatology, this concern might be partially addressed. The cutoff point of 5.7 was found to be overly sensitive in the US college population [42], so it is a reasonable threshold above which to initially allocate interventions to those potentially in need but not currently accessing services. However, future and parallel research should focus on validating the assessment tools.

Another potential limitation is the fact that the two active conditions differ both by the degree of coaching support and the program used, which precludes this study from clearly deducing the additional, if any, benefit of guidance. However, the primary hypothesis is that the use of one or both of the active interventions will lead to a greater GAD symptom reduction than the wait-list control. If the unguided program is found to be both feasible to disseminate to this population and relatively effective, future controlled studies can evaluate the comparative benefit of guidance and conduct cost-benefit analyses of delivering unguided versus guided programs. The conditions under which it is more or less effective will also be explored (eg, it might be more effective for those with higher reported motivation who are more likely to complete more of the program). The primary initial aim is an evaluation of the feasibility and efficacy of the model of survey-linked-to-online-interventions to reduce the incidence and prevalence of common mental health disorders in defined Indian university populations**.**

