### Participants and Procedures

#### Recruitment

The flowchart (Figure 1) shows the process of recruitment and follow-up of students in the trial. Potential participants will be recruited through an online survey delivered across 3 colleges in Hyderabad. The research coordinator will visit each site and deliver presentations about the study as well as send campus-wide emails. After raising awareness about the study across the campus, the research coordinator will circulate a link to an online survey via email, which will also be posted in the student Facebook page and other social media groups. The landing page will again provide information about the study and instruct interested individuals to move forward to complete an online consent form and screening survey. This landing page will also contain the contact information of the on-campus counselor, as this information is meant to be available to all students across campus.

Those who meet criteria for clinical or subthreshold GAD will be invited to participate in the study and use an online program. Those who are interested will be informed that they will be assigned to a condition within 4 weeks. Everyone will receive their assignment email within 4 weeks following baseline, and those assigned into the 2 treatment conditions may activate their program account and begin immediately. Students in the GAD Online or Lantern conditions will have access to the intervention over a 3-month period. Students assigned to GAD Online can access content at whatever pace they choose. Students assigned to Lantern can access up to1 session per day because the program is structured to build mastery. Program access will be disconnected following this period. If students still meet clinical criteria for GAD at the end of the intervention, they will receive a referral to visit the on-campus counselor. Students will also be given a list of free, publicly available online self-help resources for anxiety (eg, Mental Health Online, ThisWayUp). Continuation in the guided intervention will not be possible due to resource constraints around program coach availability in the context of this research trial. Assessments will be conducted completely online. At each assessment time point, students will receive an email with a link to an online survey hosted on Qualtrics, an online survey platform with industry-standard data security measures.

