#### Sample Size Estimation

The sample size estimation is based on detecting differences in GAD symptom severity change (measured using dimensional scoring of the GAD-Q-IV) from baseline to post- and follow-up assessments between each active conditions and the wait-list control group. Treatment trials of online, CBT-based, guided self-help interventions for GAD have found an average large effect size of roughly 1.07 relative to a wait-list control group using the GAD-Q-IV [38]. In this study, more than half of the treated participants had recovered according to a structured interview, suggesting that a treatment effect size of 1.07 is clinically meaningful. Treatment trials of purely self-help interventions for subthreshold and clinical anxiety have found smaller yet still promising effect sizes ranging from 0.62 to 0.84, respectively, relative to a wait-list control group [31].

To enable detection of difference in mean change between each active intervention and the control group, the sample size is powered to detect at least a medium effect size of 0.5. With 80% power and assuming a 5% significance level, a minimum total sample size per group of 64 is required. Assuming the GAD-Q-IV SD is 3.46 [49], the proposed sample size provides 80% power to detect a between-group effect corresponding to a GAD-Q-IV change of 1.73 points (or a Cohen’s *d* of 0.5 or greater). By targeting 100 students recruited per condition (N=300), even allowing for nearly 30% attrition, which is a possibility in Internet-based intervention trials, GAD-Q-IV mean differences between each active condition compared with the wait-list control condition will be detected with sufficient power. The difference in mean change between the two active conditions is not a primary comparison, as they are two different programs.

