### Details of the Measurements

#### Generalized Anxiety Disorder Questionnaire (4th Edition)

The primary outcome is GAD symptom severity as measured by dimensional scoring of the 4th edition of the Generalized Anxiety Disorder Questionnaire (GAD-Q-IV) [42]. GAD caseness, as measured by categorical scoring of the GAD-Q-IV, is a secondary measure. The GAD-Q-IV is a 9-item self-report measure designed as an initial screen for the presence of GAD based on the DSM-IV. The GAD-Q-IV showed 89% specificity and 83% sensitivity when compared to structured interview diagnoses of individuals with GAD, social phobia, panic disorder, and a nonanxious comparison group. The GAD-Q-IV has demonstrated good test-retest reliability in a college sample over a 2-week assessment, with 92% of the sample showing stability across time with respect to GAD diagnosis [42].

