#### Emotional Distress From Anxiety Measure

The Patient Reported Outcomes Measure Information System (PROMIS) Emotional Distress from Anxiety measure [56] is a reliable 8-item self-report measure to evaluate emotional distress from anxiety. This measure was included as a potential global outcome measure of improved quality of life.

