#### Penn State Worry Questionnaire

The Penn State Worry Questionnaire (PSWQ) [57] is a 16-item self-report measure of the frequency and intensity of worry. The PSWQ has been shown to distinguish individuals with GAD from individuals with other anxiety disorders [58]. This measure was included to assess change in worry, a primary symptom of GAD.

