### Program Use and Engagement

Program usage will be examined for the 2 active intervention groups with respect to 3 indices: frequency of logins, frequency of self-monitoring, and number of modules accessed. Reason for drop out will be assessed via self-report questions in the survey as well as a semistructured interview with those who are willing to enroll in a follow-up substudy. For both the GAD Online and Lantern platforms, module access can be passively monitored. Engagement in Lantern can be further qualified in terms of engagement with the program coach. The Lantern software can program reminders for coaches to reach out to inactive users after a specific period. Coaches are given training in motivational interviewing and encouraged to use these skills to help engage users and address fluctuating stages of change during the intervention. Unstructured data (ie, text) from users’ program entries and correspondence with coaches can be qualitatively (eg, language used) and quantitatively (eg, user: coach message frequency) evaluated, with participant consent and understanding that message content can be used for research, to examine motivational strategies and engagement.

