### Program Satisfaction

Program satisfaction will be examined for the 2 active intervention groups using the Client Satisfaction Questionnaire (CSQ) [67]. The CSQ is an 8-item self-report statement of satisfaction with health and human services. The generic questionnaire has been customized for each intervention (eg, replacing the term “service” with “the GAD Online program” or “the Lantern Anxiety Program”). Those using Lantern will also provide feedback on their experience working with the program coach.

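### The 9-item primary outcome is described only as part of one long online survey at months 3 and 9; a GAD-Q-IV-only fallback for non-responders in all arms would be a cheap safeguard

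*Protocol article*

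**What the plan says.** **One route.** Assessment is wholly online. Under Recruitment: "At each assessment time point, students will receive an email with a link to an online survey hosted on Qualtrics". No other way of obtaining the outcome is described.

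**A short primary scale in a long battery.** "The GAD-Q-IV is a 9-item self-report measure designed as an initial screen", and its dimensional score is the primary outcome. Table 1 repeats the symptom and functional scales at months 0, 3 and 9 alongside it.

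**Extra questions in the program arms at month 3.** Table 1 places program use, usefulness and satisfaction at month 3 only. Satisfaction is measured in the two program arms: "The CSQ is an 8-item self-report statement of satisfaction with health and human services". Lantern users also rate their experience with the coach (Program Satisfaction). In addition, "Reason for drop out will be assessed via self-report questions in the survey" (Program Use and Engagement).

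**Burden.** The Measures section says that skip logic lets students with low scores and fewer comorbid concerns bypass subsections. Limitations then says: "in future trials, the real and important limitation of response burden could be addressed and fewer, more targeted measures could be administered".

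**Expected loss.** Sample Size Estimation recruits 100 per arm, "even allowing for nearly 30% attrition, which is a possibility in Internet-based intervention trials". Outcome Analyses plans an intention-to-treat mixed model that keeps participants with missing data.

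**Completion condition.** Under Wait-list Control Condition, controls are given a program once they have completed the month-3 and month-9 surveys. No counterpart is described for the program arms.

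**The concern.** The primary outcome is self-reported and takes nine items, but as described a student reaches it only by opening the full survey. Someone who met that survey at baseline and will not face it again gives no primary outcome, although the nine items alone might have been answered.

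Two things are at stake. The first is precision, which the recruitment target largely protects. The second is bias in the program versus wait-list contrast, which a larger sample does not cure. Three features could tie non-response to arm or to outcome:

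- The month-3 form, at the primary end point, is longer in the program arms.
- Only wait-list students have program access tied to completing the surveys.
- Skip logic gives the longest route to students who still have high scores and comorbid symptoms. This sample is selected for GAD symptoms, and the Measures section expects comorbidity.

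The mixed model uses partial data, but does not by itself remove bias when loss depends on the unobserved outcome.

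**Working it through.** **1. The plan's own figure.** Inputs from Sample Size Estimation: difference 1.73, SD 3.46, so d = 1.73/3.46 = 0.5; power 80%; significance level 5%, taken as two-sided. The normal approximation gives n = 2 × (1.96 + 0.84)² / 0.5² ≈ 63 per group. With the noncentral t, power is 0.795 at 63 and 0.801 at 64, so the stated 64 reproduces.

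**2. Attrition allowance.** 64/0.70 = 91.4, so 92 per arm would suffice, and 100 are planned. After 30% loss, 70 remain and power is 0.836. Fewer than 64 of 100 remain only when loss exceeds 36%.

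**3. Survey length**, from the item counts under Details of the Measurements:

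| Instrument | Items |
|---|---|
| GAD-Q-IV | 9 |
| PROMIS anxiety | 8 |
| PSWQ | 16 |
| PDSR | 22 |
| SPDQ | 10 |
| PCL-5 | 20 |
| DASS21 | 21 |
| ISI | 7 |
| PROMIS social roles | 8 |
| K10 | 10 |
| GSE | 10 |
| **Sum** | **141** |
| with the 8-item CSQ (program arms, month 3) | **149** |

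The primary scale is 9/141 = 6.4% of the counted items, or 9/149 = 6.0% with the CSQ. The SDQ, the FOCI-based scale, specific fears, alcohol, medication, help seeking, grade point average, motivation, usefulness, program use and coach feedback have no stated count and come on top.

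**4. Effect of skip logic.** The article does not name the sections that can be skipped. As an illustration only, bypassing PDSR, SPDQ and PCL-5 entirely would remove 22 + 10 + 20 = 52 items and leave 141 − 52 = 89 counted items. So 141 describes the full route and is not a minimum for each student.

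**5. What a short fallback could add.** The documents give no share of loss due to survey length, so the recovered share r is an assumption. With attrition a, equal in both arms, n = 100 × (1 − a(1 − r)), rounded. Power is for d = 0.5 per comparison, two-sided 5%, noncentral t.

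| Attrition | No fallback | r = 10% | r = 25% | r = 50% |
|---|---|---|---|---|
| 30% | 70; 0.836 | 73; 0.851 | 78; 0.873 | 85; 0.900 |
| 40% | 60; 0.775 | 64; 0.801 | 70; 0.836 | 80; 0.882 |
| 50% | 50; 0.697 | 55; 0.738 | 62; 0.789 | 75; 0.860 |

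**6. Size of the counted arm difference.** It is 149 − 141 = 8 items, at month 3. Assume a constant break-off rate h per item. If these items came before the GAD-Q-IV and the GAD-Q-IV came last, the extra loss would be (1 − h)^141 − (1 − h)^149. That is 0.4 percentage points at h = 0.05% and 1.2 at h = 0.2%. If the extra items follow a saved GAD-Q-IV, they cause no break-off loss of primary data. This does not cover students who never open the survey, nor the completion condition in wait-list.

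**The case against.** Much of the case on the other side stands.

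- **Burden is not ignored.** Skip logic operates in this trial, and only a smaller battery is left to future ones. A reader might infer that every student faces at least 141 items, or that nothing is done here. The Measures section supports neither reading. What remains is that skip logic helps least those with high scores and comorbidity.
- **Instrument order is not given.** A reader might infer that the GAD-Q-IV sits deep in the survey and is lost when students break off. It may already come first. Order, saving of partial responses and reminders are survey-build details that an article commonly leaves out, so their absence is not a fault. Being first would still not reach students who never open the survey.
- **Power is adequate as planned**, and the mixed model retains partial data. This answers the precision concern at the planned attrition, but not bias from selective loss.
- **The counted arm difference is small**: 8 items, documented at month 3 only.
- **The battery is a reasoned choice.** The Measures section justifies its breadth by an epidemiological subaim, comorbidity and secondary outcomes. A fallback leaves the battery intact.
- **A short form touches other parts of the plan.** Wait-list students get a program on completing the surveys, and the Eligibility section relies on post-intervention survey feedback to give referrals. A 9-item response fits neither automatically, so the fix must address both.

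**Conclusion.** The point holds as an inexpensive improvement to how the primary outcome is collected; it is not an error in the calculations. The documents establish that the only described route is one survey with 141 counted items on the full route (149 in the program arms at month 3) plus uncounted ones. They also establish that burden is admitted, that nearly 30% attrition is allowed for, and that two features differ by arm. It follows that some primary data may be lost, possibly unequally.

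The documents do not show that data are lost because of survey length, how many, or that the arms will differ materially. They do not show that the trial is underpowered: power per comparison is 84% at 30% loss and stays at or above 80% up to 36%. The gain from 84% to between 85% and 90% rests on an assumed recovery of 10% to 50% of a 30% loss, equal in the two arms compared. The stronger reason for the change is that it can lower the missing share directly, which over-recruitment cannot do. The bias avoided cannot be sized from the documents.

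**What to change.** The Results section reports recruitment as done, so this applies to surveys not yet sent.

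1. After the full-survey reminders, send non-responders in all three arms a link to the GAD-Q-IV alone.
2. Include these responses in the primary analysis and flag them, so that their number can be reported by arm.
3. Confirm that the GAD-Q-IV comes first in the full survey and is saved when its page is submitted. If so already, one sentence saying so is enough.
4. State how a fallback response relates to the completion condition for wait-list program access, and to the referrals that depend on survey feedback. The investigators need to settle both; no rule is proposed here.

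The cost is one extra email per assessment, a short form, possibly a re-ordering of pages, and the wording for item 4. The downside is that secondary outcomes stay missing for students who answer only the fallback.

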## Abbreviations

CBT: cognitive behavior therapy
DASS: Depression Anxiety Stress Scales
DSM: Diagnostic and Statistical Manual of Mental Disorders
FOCI: Florida Obsessive-Compulsive Inventory
GAD: generalized anxiety disorder
GAD-Q-IV: 4th edition of the Generalized Anxiety Disorder Questionnaire
GSES: General Self-Efficacy Scale
ISI: Insomnia Severity Index
K10: Kessler distress measure
PCL-5: Post-Traumatic Stress Disorder Checklist for DSM-V
PDSR: Panic Disorder Self Report
PROMIS: Patient Reported Outcomes Measure Information System
PSWQ: Penn State Worry Questionnaire
RCT: randomized controlled trial
SDQ: Strengths and Difficulties Questionnaire
SPDQ: Social Phobia Diagnostic Questionnaire
